#### Secondary outcome measures

Secondary GP level outcomes include whether or not the GP provided advice on activity or bed rest or referred for any type of imaging, scores on measures of behavioural constructs (Table 2), and GPs' fear-avoidance beliefs (Table 1). Secondary patient participant level outcomes include usual pain, fear-avoidance beliefs, and whether the patient received a plain x-ray. Additionally, health-related quality of life and health service utilisation will be measured and this data used in the economic evaluation [28]. Rationale for the selection of secondary outcomes is provided in the full protocol, available on request.

**Table 2 T2:** Behavioural constructs

**Domains**	**Explanation**	**Domain measured for behaviour**	
		
		X-ray^1^	Activity^2^
Behavioural intention^3^	Whether the GP intends to engage in the behaviour.		
Generalised		✓	✓
Performance		✓	✓
Attitude^4^	Whether the GP is in favour of performing the behaviour.		
Direct		✓	✓
Indirect		✓	✓
Subjective norm^4^	How much the GP feels social pressure to engage in the behaviour.		
Direct		✓	✓
Indirect		✓	✓
Perceived behavioural control^4^	Whether the GP feels in control of the behaviour.		
Direct		✓	✓
Indirect		✓	✓
Beliefs about capabilities	Whether the GP is confident in performing the behaviour.	✓	✓
Beliefs about professional role	Whether the GP feels it is their professional responsibility to perform the behaviour.	✓	✗
Knowledge	Whether the GP has knowledge of the behaviour.	✓	✓
Memory	Whether the GP remembers to perform the behaviour.	✗	✓
Environmental context	Whether the GP feels the environmental context supports performance of the behaviour.	✗	✓

^1 ^Managing patients without referral for plain x-ray.

^2 ^Providing advice to stay active.

^3 ^Domain measured using generalised method (*e.g*., by asking GPs about their strength of intention to perform the behaviour) and performance method (*e.g*., asking GPs about how often they intend to perform the behaviour).

^4 ^Domain measured directly (*e.g*., by asking GPs about their overall attitude) and indirectly (*e.g*., by asking about specific behavioural beliefs).

Details of the number of items measuring each domain, for each behaviour, and measures of reliability and validity of the constructs are available in the full protocol.

### Data quality assurance

Details of data quality assurance for the trial are available in the full protocol. In brief, methods used to enhance the quality of the data will include: daily checking for accuracy and completion of data forms; range checks; and cross-form consistency. Double data entry will be used for the GP questionnaires (Table 1). All telephone interviews at the patient participant level will be recorded and a fraction of these will be checked using a continuous sampling plan [40,41]. In addition, a continuous sampling plan will be used to check a sample of data abstracted from patient medical records.

### Sample size

The primary process and patient outcomes are x-ray referral and LBP-specific disability as measured by the RDQ [37]. In the calculation of sample size for these outcomes, adjustment needs to be made for the clustered nature of the design. The inflation factor used to achieve this is determined from the average cluster size and the intra-cluster correlation (ICC) [42]. Empirical research has suggested ICCs of the order 0.10 for process measures and 0.05 for patient outcomes in primary care [43]. These have been used in the following calculations. It is estimated that 28% of current GP consultations for acute LBP in Australia result in a lumbar spine x-ray [7]. Interventions comparing standard CPG dissemination with no intervention control groups have shown improvements in care of approximately 8% [2]. We therefore anticipate a decrease in the percentage of x-ray prescription in the control group of this magnitude. We consider a reduction of 10% to be clinically important. Therefore, if the percentage of x-ray prescription at the end of the study in the control group is 20%, a sample size of 37 general practices per arm, with an average of 25 patients per practice, will be sufficient to detect an absolute decrease in the percentage of x-ray prescription of 10% (to 10%) or more with 90% power. This assumes a significance level of 5% and an ICC = 0.10.

This sample size will be sufficient to detect a clinically important difference of at least two points between groups in the RDQ with at least 99% power, assuming a standard deviation of six [44,45], significance level of 5%, and an ICC = 0.05.

Allowing for 20% attrition in practices (equivalent to 450 patient participants), we plan to initially recruit 46 practices per arm, with an average of 25 patients per practice, providing a total of 2,300 patients. These sample size calculations are likely to be conservative because, due to a lack of prior information, stratification has not been incorporated into the calculations.

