The management of people with acute LBP in general practice has been shown to have only reasonable concordance to CPG-recommended management in Australia [7]. Despite being well informed about, and agreeing with, acute LBP guidelines, many primary care practitioners do not adhere to their recommendations [8-12]. Reasons cited for non-adherence in these studies include patients' preference for non-evidence-based care (*e.g*., x-rays) and lack of generalisability to general practice.

The aim of the CPG is to inform clinicians of the appropriate management of acute non-specific LBP. Acute non-specific LBP is defined by the guideline as pain present for less than three months, located in the lumbar and/or sacral regions of the spine with no 'red flags' present [3]. We have chosen two key messages from the CPG to target for this study that we consider are representative of the guideline as a whole. One relates to diagnosis of acute LBP and states that diagnostic x-rays are rarely necessary. Plain x-rays for acute non-specific LBP are of limited diagnostic value, expose people to unnecessary ionising radiation, and provide no benefits in physical function, pain, or disability [3]. This key message was chosen because there is evidence that plain x-rays are over utilised in the management of acute LBP in general practice. In Australia, 28% (95% confidence interval: 18% to 39%) of patients with acute LBP receive an x-ray [7] and up to 48% in the United States and Europe [8-10,13,14]. There is also wide variation of x-ray utilisation among GPs [14]. The other key message relates to providing advice to remain active. This key message was chosen because it is the only recommended therapy in the CPG with Level I evidence.

Implementing change in practice has been attempted by a number of direct and indirect methods [2]. While our project will utilise direct methods, including GP education, indirect methods such as mass media campaigns have been previously conducted and evaluated in Victoria, Australia [15-18].

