### Randomisation and allocation concealment

General practices meeting the inclusion criteria will be randomly allocated to receive either the intervention or control. Restricted randomisation will be used to reduce the probability of baseline imbalance. Within stratum, one-half of the practices will be randomised to the intervention group, and the other half to the control using computer-generated random numbers. Four strata will be defined by the number of GPs per practice (two levels) and whether the practice is in a rural or metropolitan area. A statistician independent of the study will implement the randomisation. They will be provided with only general practice codes and stratification variables. Allocation will be concealed from the investigators until baseline data has been collected from GPs.

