Estimates of intervention effect from these models will yield odds ratios. For interpretability, we plan to also provide estimates of risk ratios using a simple formula that will utilise the odds ratios estimated from these models [59]. For each outcome, the estimate of intervention effect and its 95% confidence interval will be provided. For the primary outcomes we plan to provide estimates of the coefficient of ICC and their 95% confidence intervals.

No adjustment will be made for multiple testing. All tests will be two-sided and carried out at the 5% level of significance.

Any future change to the statistical methods outlined in this analysis strategy will be documented with full justification as an amendment to the full protocol.

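### The x-ray power of 90% is calculated as if every practice supplied 25 patients, so describing it as likely conservative, on stratification alone, is not supported

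*Protocol article*

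**What the plan says.** The Sample size section sizes the trial on x-ray referral. It assumes 20% in the control arm, an ICC of 0.10 and an average of 25 patients in each of 37 practices per arm, and claims to detect "an absolute decrease in the percentage of x-ray prescription of 10% (to 10%) or more with 90% power". On clustering it says: "The inflation factor used to achieve this is determined from the average cluster size and the intra-cluster correlation (ICC"). No variation in practice size enters. Recruitment is set at 46 practices per arm to allow for 20% attrition of practices. The section closes with an assessment of its own calculation: "These sample size calculations are likely to be conservative because, due to a lack of prior information, stratification has not been incorporated into the calculations".

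Other sections bear on practice size. Trial design defines a cluster as a practice with one or more GPs. Randomisation and allocation concealment says: "Four strata will be defined by the number of GPs per practice (two levels"), crossed with rurality. Recruitment of patient participants leaves it to each patient to start enrolment. Primary analysis plans GEEs with an exchangeable correlation and robust variance, adjusted for the stratifiers, and states: "All tests will be two-sided and carried out at the 5% level of significance".

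The 20% control rate is 28% less about 8 points expected from guideline dissemination. The 28% is described in two ways, with the same reference cited. The Background has "28% (95% confidence interval: 18% to 39%) of patients with acute LBP receive an x-ray"; Sample size has "It is estimated that 28% of current GP consultations for acute LBP in Australia result in a lumbar spine x-ray".

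**The concern.** An inflation factor built on the mean cluster size is exact only when clusters are equal. Unequal clusters carry less information for the same total number of patients, so the omission can only lower power. Here a single-GP practice and a large group practice both count as 25 patients. The protocol names one omitted factor that would help (stratification), leaves out one that would hurt, and concludes that the calculation errs on the safe side.

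X-ray referral fixes the trial's size; the disability outcome has more than 99% power. A null x-ray result would therefore be read as coming from a trial with at least 90% power, and the word conservative invites readers to assume more.

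**Working it through.** **Inputs from the protocol article (Sample size, Primary analysis).** Two-sided 5%; 20% v 10%; ICC 0.10; mean m = 25; 37 practices per arm analysed, 46 recruited.

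**Assumption.** The CV of patients per practice is not given. I use 0.4, 0.65 and 0.8.

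**1. Reproducing the stated figure.**
- Design effect: 1 + (25 − 1) × 0.10 = 3.4.
- Individually randomised sample for 90% power (pooled two-proportion test, no continuity correction): 266 per arm.
- Practices: 266 × 3.4 / 25 = 36.2, rounded up to 37.
- Effective n at 37 per arm: 37 × 25 / 3.4 = 272.1. Power = Φ[(0.10 − 1.96 × √(2 × 0.15 × 0.85 / 272.1)) / √((0.16 + 0.09) / 272.1)] = Φ[(0.1000 − 0.0600) / 0.0303] = Φ(1.32) = 90.6%.
- At 36 per arm the same formula gives 89.9%, so 37 is the smallest number that reaches 90%.

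The arithmetic is correct on its own inputs.

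**2. Allowing for unequal practices.** Two allowances bracket the answer.

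(a) Standard unequal-cluster design effect: 1 + ((CV² + 1) × 25 − 1) × 0.10. It suits an analysis that does not weight practices according to the ICC.

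(b) Relative efficiency under exchangeable weighting: RE = 1 − CV² × L × (1 − L), with L = 2.5 / (2.5 + 0.9) = 0.735 and L(1 − L) = 0.195. The design effect is then 3.4 / RE. This matches the planned GEE.

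| CV (assumed) | (a) design effect | (a) power, 37 / 46 per arm | (b) RE | (b) design effect | (b) power, 37 / 46 per arm |
|---|---|---|---|---|---|
| 0 | 3.40 | 90.6% / 95.5% | 1.000 | 3.40 | 90.6% / 95.5% |
| 0.4 | 3.80 | 87.3% / 93.3% | 0.969 | 3.51 | 89.8% / 95.0% |
| 0.65 | 4.46 | 81.6% / 89.1% | 0.918 | 3.71 | 88.1% / 93.9% |
| 0.8 | 5.00 | 77.1% / 85.4% | 0.875 | 3.88 | 86.6% / 92.8% |

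Practices per arm needed for 90% power are 41, 48 and 54 under (a), and 38, 40 and 42 under (b). The 46 column applies only if no practice is lost. The protocol reserves the difference for attrition (46 × 0.8 = 36.8), so 37 is the planning case.

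**3. Dependence on the control rate (secondary).** Fixed 10-point fall, equal practices, 37 per arm, design effect 3.4:

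| Control v intervention | Power |
|---|---|
| 18% v 8% | 93.6% |
| 20% v 10% | 90.6% |
| 25% v 15% | 83.2% |
| 28% v 18% (no control-arm fall) | 79.3% |
| 31% v 21% | 75.9% |

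Taking 8 points off the Background's interval of 18% to 39% gives control rates from 10% to 31%, with midpoint 20.5%. The planned 20% is therefore central. At the 10% end a 10-point fall would mean no x-rays at all.

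**The case against.** The strongest reply is that nothing is miscalculated and the loss is small under the analysis actually planned. Both points stand. The 37 and the 90% reproduce, and an exchangeable GEE recovers most of the efficiency that allowance (a) gives away: at CV 0.65 it costs 2.5 points of power, not 9. Every CV here is assumed. The gain from stratification and covariate adjustment, though unquantified, might offset a loss of that size. The article is also abridged, and sensitivity tables may be in the full protocol. None of this rescues the conservative claim, which the article makes itself and supports with one factor of unknown size. The net direction is simply not known.

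A reader might go further and infer that true power is only 70 to 85%, or that 20% was picked as a favourable control rate. The documents do not support either. Falling below about 87% within this CV range takes either a weighting that is not planned or a control rate well above 20%. Combining 28% v 18% with CV 0.65 gives 68% under (a) or 76% under (b), but it supposes that dissemination has no effect, contrary to the plan's stated premise. The 20% is openly conditional ("if the percentage of x-ray prescription at the end of the study in the control group is 20" per cent), sits near the middle of the range implied by the cited interval, and power rises below it.

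A reader might also infer that the per-consultation wording of the 28% is the wrong one. Which wording matches the source cannot be settled here, and neither changes a number in the calculation.

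**Conclusion.** The point holds in a limited form. There is no arithmetic error. The stated power is the equal-practice figure, with 0.6 of a point to spare, in a design whose practices will almost certainly differ in size. For an assumed CV of 0.4 to 0.8 the loss at 37 per arm is about 1 to 4 points under the planned GEE (to 90–87%), and about 3 to 14 points under the standard design effect (to 87–77%). If all 46 practices per arm were retained, the GEE figures would stay at about 93 to 95%. These results rest on the protocol's ICC, mean size and 20% v 10%, and on the assumed CVs. The description of the calculation as likely conservative is unsupported. Sensitivity to the control rate runs both ways and belongs in a sentence of context, not in a charge of error.

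**What to change.** In the Sample size section:

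1. Delete the statement that the calculations are likely conservative, or qualify it by saying that unequal practice sizes act in the opposite direction and that neither effect has been quantified.
2. State an assumed CV of patients per practice and its basis. Restate the x-ray power with an unequal-cluster allowance matched to the exchangeable GEE, at 37 and at 46 practices per arm.
3. Add one sentence saying that, for a fixed 10-point fall, power depends on the control rate in both directions, for example 93.6% at 18% v 8% and 79% at 28% v 18% with equal practices and 37 per arm.
4. Describe the 28% in the same way in Background and Sample size, after checking the cited source, and say how it relates to referral per patient over three months.

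The cost is a few sentences and a slightly less favourable stated power. No extra patients and no change of design are needed.

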### Analyses

#### Analysis subsets

The primary analysis of the data in this CRCT will be analysed using the principle of intention-to-treat (ITT). This is appropriate for a CRCT such as ours, since an analysis which allows for non-compliance by GPs and patients is more likely to provide an estimate of intervention effect that is more reflective of actual clinical practice [46,47].

Requirements for an ideal ITT analysis are: full compliance with the randomised intervention; no missing responses; and follow-up on all participants [46]. In a CRCT the potential for non-adherence to the intervention and loss to follow-up are more complex than an individual RCT, because it can occur at multiple levels. For example, in our CRCT, GPs within general practices may not comply with the intervention, GPs may withdraw, and even general practices may discontinue participation. At the patient level, there may also be non-adherence to advice provided by the GP, patient withdrawal or loss to follow-up.

Non-adherence to the intervention is likely to reduce its potential effectiveness, and provide a conservative estimate of intervention effect compared to what would be expected if there was full compliance [46]. Loss to follow-up is likely to lead to biased estimates of intervention effect, particularly when there is differential drop out between intervention arms that is related to the intervention itself. We plan to implement procedures to minimise loss to follow-up and withdrawal at the patient, GP, and general practice level. Additionally, through modelling, we will investigate the effect of missing data (details available in the full protocol). Where possible, we will collect information on reasons for patient, GP, and general practice withdrawal.

For the primary outcomes (Table 1), a secondary per-protocol analysis will be carried out to estimate the effect of the intervention for the subgroup of GPs who complied with the intervention. Compliance to the intervention is defined as attendance of at least one workshop.

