**Methods/Design:**

This study protocol describes the details of a cluster randomised controlled trial. Ninety-two general practices (clusters), which include at least one consenting general practitioner, will be randomised to an intervention or control arm using restricted randomisation. Patients aged 18 years or older who visit a participating practitioner for acute non-specific low back pain of less than three months duration will be eligible for inclusion. An average of twenty-five patients per general practice will be recruited, providing a total of 2,300 patient participants. General practitioners in the control arm will receive access to the guideline using the existing dissemination strategy. Practitioners in the intervention arm will be invited to participate in facilitated face-to-face workshops that have been underpinned by behavioural theory. Investigators (not involved in the delivery of the intervention), patients, outcome assessors and the study statistician will be blinded to group allocation.

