### Blinding

Investigators (not involved in the delivery of the intervention), patients, outcome assessors, and study statistician (JM) will be blinded to group allocation until the statistical analysis has been completed. Due to the nature of the intervention, it is not possible to blind the GPs to group allocation. However, the GPs will only be told that they are to receive one of two interventions, one being information only and the other attending facilitated small group educational workshops. The success of blinding will not be evaluated.

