### Interventions

#### Control group

The control group will receive access to the guideline as per the CPG's existing dissemination strategy. A printed copy of the guideline and a written reminder of how to access the electronic version of the CPG will be sent to control group practices.

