The intervention will consist of a combination of behaviour change techniques. These techniques will be utilised throughout the workshops including providing instruction; modelling/demonstrating the behaviour by a peer expert; providing information on consequences; prompt barrier identification; time management; prompt specific goal setting; rehearsal; persuasive communication; and scripting [32]. These specific techniques have been chosen because they are considered the best approach to address the barriers and enablers to the CPG's implementation [33]. The intervention will concentrate on delivering the CPG's key messages, namely that diagnostic x-rays are rarely necessary in the management of acute LBP and that advising patients to remain active reduces pain and disability. The intervention will consist of facilitated face-to-face small group workshops. There will be a pre-course reflective activity where the GPs will document their management of a series of patients that present to them with acute LBP over the two weeks preceding the workshop. There will be two workshops of three hours each, or one workshop of six hours depending on the preference of the GP. These workshops will be directed by a trained GP facilitator and will involve a combination of didactic lectures and small group discussions. A detailed description of the targeted implementation strategy, including the development process, will be reported in a separate publication. We also plan to evaluate the fidelity of delivery of the intervention to assess the extent to which the intervention, as delivered, was faithful to the intervention as planned [34]. A mixed-methods approach will be employed based on a recent project that evaluated fidelity of delivery of a physical activity intervention [35]. We plan to report this evaluation in a separate publication.

For GPs in the intervention group who cannot attend the workshops, a DVD will be provided to them. The DVD will include film footage of the workshops and electronic resources related to LBP management.

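### The planned per-protocol analysis restricts one arm to GPs who attended a workshop, so it is a non-randomised contrast and does not in general give the effect in compliers

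*Protocol article*

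**What the plan says.** Intention-to-treat (ITT) is the primary analysis. For the two primary outcomes (x-ray referral and the Roland-Morris score, RDQ), Analysis subsets adds a secondary per-protocol analysis to "estimate the effect of the intervention for the subgroup of GPs who complied with the intervention". The rule follows directly: "Compliance to the intervention is defined as attendance of at least one workshop". The article names neither the comparison group nor the estimator for this analysis.

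Four other places bear on it:

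- **Attendance is voluntary.** Abstract, Methods/Design: "Practitioners in the intervention arm will be invited to participate in facilitated face-to-face workshops".
- **Format.** Intervention group: "There will be two workshops of three hours each, or one workshop of six hours depending on the preference of the GP".
- **Non-attenders still receive something.** Same section: "For GPs in the intervention group who cannot attend the workshops, a DVD will be provided to them". The DVD holds film of the workshops and electronic resources.
- **Controls are offered no workshop.** Control group: "A printed copy of the guideline and a written reminder of how to access the electronic version of the CPG will be sent to control" practices.

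Under Blinding, the study statistician is among those who "will be blinded to group allocation until the statistical analysis has been completed".

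**The concern.** The quantity named is the effect among GPs who comply. To estimate it, the attenders' patients must be compared with the patients of control GPs who would have attended if invited. Those control GPs cannot be identified: they were never invited, and the compliance rule has no meaning in their arm. The obvious reading of the plan is therefore attenders against all controls. That sets a self-selected part of one randomised arm against the whole of the other.

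GPs who find time for six hours of education on back pain may already refer for x-ray at a different rate from those who do not. Any such difference enters the contrast as if it were an intervention effect. The result could show a benefit where there is none, or hide one, yet be reported as the effect in compliers for both primary outcomes.

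**Working it through.** **The plan's own figure.** The article gives no figure for the per-protocol analysis. Its sample size supplies the control rate and target used below, and it reproduces. For 20% against 10%, two-sided 5% and 90% power, 266 patients per arm are needed before clustering. The design effect is 1 + (25 − 1) × 0.10 = 3.4, and 266 × 3.4 / 25 = 36.2, rounded up to the stated 37 practices per arm.

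**Inputs.**

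- From Sample size: control x-ray rate 20%, target reduction 10 points, ICC 0.10.
- Assumed, because the documents give neither: c, the share of intervention-arm patients whose GP attended (0.5 to 0.9); and d, the excess x-ray rate, absent any intervention effect, among patients of non-attenders over patients of attenders (2 to 10 points).

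**Bias with no true effect.** Let a be the attenders' underlying rate. Randomisation makes the whole intervention arm average 20%:

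c × a + (1 − c) × (a + d) = 20, so a = 20 − (1 − c) × d.

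Attenders minus all controls is then a − 20 = −(1 − c) × d. Spurious reduction in points:

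| c | d = 2 | d = 5 | d = 10 |
|---|---|---|---|
| 0.5 | 1.0 | 2.5 | 5.0 |
| 0.7 | 0.6 | 1.5 | 3.0 |
| 0.9 | 0.2 | 0.5 | 1.0 |

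If attenders refer more often than non-attenders, d is negative and the signs reverse. The same formula holds for the RDQ, with d in RDQ points.

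**Is d of 2 to 10 points conceivable?** An ICC of 0.10 at a 20% rate implies a between-practice standard deviation of √(0.10 × 0.20 × 0.80) = √0.016 = 0.126, or 12.6 points. The assumed range is 2/12.6 = 0.16 to 10/12.6 = 0.79 of that. This shows that the range fits the plan's own variability. It does not show that attenders and non-attenders differ by that much.

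**With a true effect.** Take a 10-point reduction in compliers, no effect in non-attenders, c = 0.7 and d = 10.

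- Attenders: 20 − 0.3 × 10 = 17% without the intervention, and 17 − 10 = 7% with it.
- Attenders against all controls: 7 − 20 = −13 points, an overstatement of 3.
- ITT effect: 0.7 × 10 = 7 points. Dividing by c gives 7 / 0.7 = 10 points, the true value.

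**What the instrumental estimate depends on.** Suppose allocation lowers the rate by e points among non-attenders' patients, through the DVD or an attending colleague. With complier effect D, the ITT effect is c × D + (1 − c) × e, so

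ITT / c = D + e × (1 − c) / c.

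The overstatement is 1.0 × e at c = 0.5, 0.43 × e at c = 0.7 and 0.11 × e at c = 0.9. If D and e are both zero, the estimate is centred on zero whatever the value of d. The assumption affects the size of an effect; selection alone does not create one.

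**The case against.** The strongest reply is that the article abridges a fuller protocol, that the analysis is secondary, and that ITT is primary and justified at length. Not setting out the estimator for a secondary analysis in an article is no fault. That stands, but the article does print both the aim and the rule, and together they create the problem.

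Several stronger readings are tempting, and the documents do not support them:

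- **That the plan specifies attenders against all control GPs.** It names no comparator. The inference is strong, because the rule cannot be applied to controls, but it is an inference.
- **That the analysis cannot estimate the effect in compliers.** It could, if covariates removed every relevant difference between attenders and non-attenders. Primary analysis commits to adjusting for the stratification factors and a fixed list of confounders. Whether the per-protocol model carries them is not shown, and nothing suggests that they would suffice.
- **That the compliance rule treats half the programme as full exposure.** One six-hour workshop is the whole programme. Only a GP on the two-session format who misses one session has three of six hours, and the article calls such a GP compliant, not fully exposed. A six-hour rule would also harm an instrumental analysis: GPs with three hours would be classed as untreated.
- **That attenders are the low-referring GPs.** The article describes non-attenders only as unable to attend. The direction of selection is unknown.
- **That the analysis contradicts the blinding statement.** That statement can be read as covering the main analysis, with this one run afterwards. Attendance data do reveal the arm, so the issue is the order of work.

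The DVD is a fair objection to the remedy. Non-attenders receive a version of the workshop, so assuming no effect in them is doubtful. As the working shows, this can inflate the estimate but does not turn selection into an apparent effect.

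**Conclusion.** The point holds. An analysis restricted to workshop attenders in one arm is not protected by randomisation and does not in general deliver the quantity that Analysis subsets says it will estimate.

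On assumed values of c and d, the error with no true effect is about 0.2 to 5 points of x-ray referral against a 10-point target. Its sign depends on who attends. These figures show what selection of a given strength would do; they do not predict what will happen in this trial.

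A reader might infer that the trial's main conclusion is at risk. It is not: ITT is primary, and neither its inference nor the sample size depends on this analysis. The change is worth making because it is cheap and concerns both primary outcomes.

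**What to change.** Replace the secondary compliance analysis with a complier average causal effect analysis, using random allocation as the instrument and keeping the plan's own rule of any workshop attendance. As described, controls have no workshop access, so non-compliance is one-sided. The estimate is the ITT risk difference (or RDQ mean difference) divided by c, with standard errors clustered by practice. The planned logit model yields odds ratios, so the risk difference has to be derived from it or estimated directly.

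Also:

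1. State the exclusion restriction: allocation has no effect on patients whose GP did not attend. Say that the DVD and influence between colleagues in one practice strain it, that the estimate is too large if they help, and vary the effect in non-attenders in a sensitivity analysis.
2. If attenders against controls is kept, label it as a non-randomised comparison and name the comparator and adjustment.
3. Run the analysis only once the blinded ITT analysis is final.

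The cost is analysis wording, an explicit assumption and a wider interval. Treating c as known, the interval is 1/c times the ITT width, for example 1/0.7 = 1.43 times at c = 0.7. No change to data collection, sample size or the primary analysis follows.
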